# A protocol for a cluster-randomized controlled trial of a self-help psycho-education programme to reduce diagnosis delay in women with breast cancer symptoms in Indonesia

**DOI:** 10.1186/s12885-017-3268-7

**Published:** 2017-04-20

**Keywords:** Breast cancer, Delay in diagnosis, Psycho-education, Self-help, Indonesia

## Abstract

**Background:**

Breast cancer (BC) is the most frequent cancer occurring in women across the world. Its mortality rate in low-middle income countries (LMICs) is higher than in high-income countries (HICs), and in Indonesia BC is the leading cause of cancer deaths among women. Delay in breast cancer diagnosis negatively impacts cancer prognosis. Only about 30% of patients who come to the hospital to check on their breast abnormalities, continue thorough examination to biopsy to get a diagnosis based on the results of anatomical pathology. Many Indonesian women with breast cancer were already in an advanced stage when starting treatment. Therefore, delay in diagnosis is a serious problem that needs to be addressed. The present study will investigate whether our newly developed self-help psycho-educational programme, “PERANTARA”, for women with breast cancer symptoms is effective to reduce patient diagnosis delay in Indonesia.

**Methods:**

A cluster-randomized controlled trial will be conducted in 106 patients in four hospitals in Bandung, West Java, Indonesia. Data will be collected at baseline (pre-assessment), 7 days after the intervention (post-assessment), and at 3 months (follow-up assessments). The primary outcome is delay in diagnosis and treatment. Secondary outcomes are breast cancer knowledge, anxiety and depression, and quality of life. Exploratively, adherence with treatment will be measured too. Data will be analysed by hierarchical linear modelling (HLM) to assess differential change over time.

**Discussion:**

If proven effective, PERANTARA will be evaluated and implemented in a diversity of settings for local cares (such as in POSYANDU, PUSKESMAS) that provide health education/psycho-education for women with breast symptoms.

**Trial registration:**

ISRCTN12570738. Date: November 19th, 2016.

**Electronic supplementary material:**

The online version of this article (doi:10.1186/s12885-017-3268-7) contains supplementary material, which is available to authorized users.

## Background

Breast cancer (BC) is the most frequent cancer occurring and the leading cause of cancer-related deaths in women, with an estimated 1.67 million new cancer cases diagnosed and 522,000 deaths in 2012 [1]. The incidence of breast cancer in LMICs is lower as compared to HICs (25.8 vs 95 per 100.000), but a major concern in LMICs is the higher mortality despite its lower incidence (12.7 vs 17.1 per 100.000) [2]. In Indonesia, BC is the most prevalent cancer among women with an incidence rate of 48,9 and a mortality rate of 19,8 women per 100,000 [3].

One of the reasons for the high mortality of breast cancer in LMICs is the fact that most cancer in LMICs is detected at later stages. Review on delay of diagnosis revealed that more than 70% of breast cancer patients in most HICs are diagnosed in Stages I and II, compared with only 20 to 50% of patients in the majority of LMICs [4]. In Indonesia, about 60%–70% of patients had their first BC-related visit to the hospital when the disease was already in advanced stages (III and IV) [5–7].

Diagnosis delay, the time between seeking medical advice and the date of final diagnosis based on pathological examination (i.e. biopsy), remains a serious problem. Studies have shown that diagnosis delay of over 3 months is associated with a bigger tumour size, positive lymph nodes, high incidence of late clinical stages, and metastatic disease [8, 9]. Delay in diagnosis predicts worse clinical outcomes [10]. The delay may cause mortality of the patient. A previous qualitative study involving 50 BC patients in Indonesia found that 35 participants (70%) were delayed in seeking help, with the time of delay ranging from 4 to 24 months, except for the four participants who had delayed for 4 years, 10 years, 3 years, and 15 years, respectively [11].

Previous studies found that delay in diagnosis among women with breast cancer symptoms was a result of a complex interaction of several factors, which often concern characteristics of the patients and the health care system. Several studies state that patients-related factors are a major concern and need to be addressed in an intervention program (e.g. lack of knowledge and awareness about breast cancer). For example, a study in Moroccan women found that diagnosis delay is also a very important health problem in Moroccan women, particulary caused by a lack of knowledge, information and awareness regarding breast cancer [12].

As diagnostic delay is a serious problem, efforts to reduce delay are necessary. Improving knowledge of women, via training and involving physicians and other healthcare providers, seems to be an effective approach to reduce delay in the diagnosis of breast cancer [13]. The delay to consult a doctor for seeking help after the discovery of the symptoms is most likely caused by lack of awareness and inadequate knowledge about symptoms and treatment of BC [11, 14, 15]. It is crucial that the information that is provided by the medical staff, is both informative and acceptable to patients.

A cross-sectional study in 70 breast cancer patients in Indonesia showed also that many breast cancer patients in Indonesia were not satisfied with the information they received [16]. The study showed that most patients were dissatisfied with the information about social support. Furthermore, the study found also that most of the patients were dissatisfied with the amount of written information. Therefore, the use of clear, concise, and easy to understand educational materials (e.g.: leaflets, posters, flipcharts table, visualized story telling) may be effective and efficient in complementing the verbal information that is usually provided by the oncologists at the oncology clinic. The utilization of educational material may be a solution to overcome the lack of resources (e.g. : experts, time and finance) and can be given by a face-to-face breast health education, either individually or in groups.

Numerous psycho-educational interventions have been designed for women (affected by) with breast cancer (or breast cancer symptoms) in response to the need for psychological support and health behavior education. A randomized controlled trial (an experimental pretest-posttest control group design) involving 76 women with BC in Turkey comparing a psycho-education program to treatment as usual reported that the psycho-educational program (which consisted of eight 90 min weekly sessions on basic information about breast cancer, nutrition, psychosocial factors, interpersonal skills, problem solving, experience sharing and support) led to positive changes in levels of adjustment to cancer [17]. In that study, the psycho-educational group had higher levels of fighting spirit, lower levels of helplessness/hopelessness, anxious preoccupation and fatalism, both at 6 weeks and 6 months after the intervention. However, there were no changes in the levels of avoidance/denial compared to the control group. Another study (one group pre-post test design) carried out in early-stage BC patients in Italy found that a psycho-educational intervention was feasible and useful to enhance coping strategies in patients [18]. An RCT that evaluated the efficacy of a psycho-educational intervention (an individualized fatigue education and support program delivered in the clinic and by phone over three 10- to 20-min sessions 1 week apart) in improving BC-related fatigue compared to general cancer educational sessions (equivalent in number and timing to the sessions that were provided for the intervention group) suggests that women who received the intervention received some short-term benefit in terms of minimization of the intensity and impact of fatigue on daily life [19]. A systematic review and meta-analysis to evaluate the effectiveness of psychosocial and especially psycho-educational support interventions for early-stage breast cancer patients showed that these interventions were effective in increasing emotional well-being [20]. An intervention study that aimed to assess the effectiveness of psycho-education on well-being status and depression among Malaysian BC patients using cluster non-randomized trial design found that group psycho-education not only significantly improved breast cancer survivors’ well-being status but also reduced depression level [21].

Web-based programs are a promising new way to offer psycho-educational interventions to patients and their caregivers [22], but several patient groups in Indonesia have no access to it, particularly patients with low education, low socio-economic status (SES) and those in rural areas. Currently in Indonesia, printed and on-line information materials about BC have been provided by hospitals, the Ministry of Health and a number of foundations or communities. However, these sources of information appeared to not have achieved an optimal impact either, due to the lack of capacity to access them, particularly for patients with low socio-economic status (SES) in rural areas. Meanwhile, the information that is accessible to the wider public (TV, radio, and newspapers) often contains promotion of traditional healing methods which even can make patients hesitant in following the process of examination (and possible treatment) at the regular hospital.

Summarizing, several educational interventions for breast cancer patients exist, but these focus mainly on coping with cancer. Interventions which focus on the reduction in diagnosis delay, are less common, and absent in Indonesia. Therefore, an educational program to diminish diagnosis delay can be of paramount importance for reducing morbidity and death. For this purpose, we developed a psycho-educational intervention (‘PERANTARA’) focused on reducing diagnosis delay.

The aim of this study is to evaluate the effectiveness of PERANTARA in reducing the delay of breast cancer diagnosis in women who visit the hospital with BC symptoms prior to formal BC diagnosis based on pathological examination. As a secondary aim, we studied its effect on breast cancer knowledge, anxiety and depression, and quality of life. Finally, we explored the effects on the longer term, also regarding the treatment delay.

## Methods

### Design

The study will be a multicentre, cluster-randomized controlled trial (cRCT), with hospitals as the unit of randomisation (clusters). We will include four hospitals in Bandung, Indonesia that have agreed to participate in this study. Because of the limited number of hospitals, we will use a cross-over design in which in each hospital will be given PERANTARA or control (treatment as usual (TAU)) at successive periods. Because every hospital forms its own control, the cross-over design can produce results with a smaller sample size than required with a parallel design. The order in which the hospital receives PERANTARA is randomly determined. The study will compare the PERANTARA to TAU in women with suspected breast cancer. This study uses two predefined periods. In the first period, two hospitals will have the experimental group (the patient is given the intervention and TAU) and two other hospitals will have the control group (patients only receive TAU). In the second period, it is the other way around.

The primary outcome is diagnosis delay in terms of the time between the date of the first consultation at the hospital and the date of final breast cancer diagnosis based on pathological examination. Secondary outcomes are breast cancer knowledge, anxiety and depression, and quality of life, as well as treatment delay.

### Participants

This study will include 106 patients in the cRCT, 53 participants in the Treatment-as-Usual (TAU) control group and 53 participants in the experiment/intervention group. Power calculations suggest a minimum sample size of 41 participants per group (power = 0.80, alpha = .05 two-sided). Taking into account 30% attrition at follow-up, at least 106 participants (53 per group) need to be included. Participants will be recruited from four district hospitals in Bandung, West Java, Indonesia, that are representative for the health care facilities in the different areas in Bandung, Indonesia.

Participants will be new patients (outpatients) who visit the hospital with breast symptoms, which make them suspects of having breast cancer. Patients eligible for the intervention program will be asked to take part in the study when reporting at the district hospitals. The following inclusion criteria will be used: women with age > 18 years, an adequate command of the Indonesian language and no major psychiatric disorder. The last is determined by checking the medical record on a consultation history/record with the Psychiatric Department. Patients who have been seen by psychiatrists are excluded from the study.

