**Fig. 1 Fig1:**
[figure not shown]
Flowchart of The Procedure

Participants in the control group will receive treatment as usual (TAU), while the intervention group will receive the PERANTARA package (which consists of printed and audiovisual materials). Participants will be requested to read and watch the intervention package within 7 days.

The post-intervention assessment will take place 7 days after the intervention. Participants will be asked to fill in the following questionnaires: (1) the Diagnostic Delay Questionnaire; Quality of Life (2) WHOQOL-Bref and (3) EQ-5D 5L; (4) HADS; (5) BCKT; (6) Intervention Material Feedback Form.

The follow up assessment will be scheduled at 3 months (12 weeks) after the post-intervention assessment. The Participant will be requested to fill in: (1) The Diagnostic Delay Questionnaire; Quality of Life (2) WHOQOL-Bref and (3) EQ-5D 5L; (4) HADS; (5) BCKT. The researcher will review the medical record of the patient to registrate the occurence of treatment delay. This period is chosen because it is also a criterion for treatment delay.

Trained research assistants with a background of psychology will conduct the assessments. All research assistants have received a 5-days workshop covering how to administer the instruments, information on common psychosocial needs of breast cancer patients, general interview techniques, and how to take a neutral role instead of a therapeutic role. Ongoing monitoring will be conducted through regular supervision by the main researcher (HS) supervised by the principle investigators.

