### Instruments

#### Primary outcome

Diagnosis delay will be the primary outcome measure. This is defined as the time between the date of the first consultation at the hospital and the date of the definite breast cancer diagnosis based on pathological examination. This outcome will be measured using the Diagnostic Delay Interviewer Guide. This instrument has been developed by the researchers and consists of the following questions: (a) What was the date that you consulted with a doctor in the hospital?, (b) What was the date that you received the breast cancer diagnosis?, and if there was a consult delay (c) What were the reasons for delay? A distinction will be made between delay due to the patient and due to the doctor. This tool will be pilot-tested before the final data collection is done.

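### The stated 80% power allows only for attrition, although the primary outcome needs a pathology-based diagnosis date and the protocol's own background figure is that about 30% of presenting patients go on to biopsy

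*Protocol article*

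**What the plan says.** Under Participants, the protocol article states: "Power calculations suggest a minimum sample size of 41 participants per group (power = 0.80, alpha = .05 two-sided"). It continues: "Taking into account 30% attrition at follow-up, at least 106 participants (53 per group) need to be included". Attrition is the only allowance. No outcome, effect size, standard deviation or test is given for the 41.

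Under Primary outcome, diagnosis delay is "the time between the date of the first consultation at the hospital and the date of the definite breast cancer diagnosis based on pathological examination". The Design section gives the same endpoint. Women are enrolled on symptoms, before any such diagnosis: "Participants will be new patients (outpatients) who visit the hospital with breast symptoms, which make them suspects of having breast cancer".

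The abstract's Background gives the share of presenting patients who get far enough to have a pathology result: "Only about 30% of patients who come to the hospital to check on their breast abnormalities, continue thorough examination to biopsy". This figure does not appear in the sample-size paragraph.

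On timing, "The follow up assessment will be scheduled at 3 months (12 weeks) after the post-intervention assessment". The Analysis plan specifies a hierarchical linear model for delay. It does not mention censoring or any time-to-event method.

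**The concern.** A woman who is never biopsied has no end date, so her delay cannot be computed. If most women who present do not reach biopsy, most of those enrolled will have no value for the primary outcome, however well they are followed. The sizing treats 41 participants as if they were 41 delay observations. The protocol's own rationale suggests that far fewer will be available.

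Diagnosis delay is the reason for the trial. If true power is well below 80%, a non-significant result is likely even when the assumed effect is real, and it could be misread as evidence that PERANTARA does not shorten delay.

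**Working it through.** **Inputs from the protocol article.** Two-sided alpha 0.05, power 0.80, 41 per group, 30% attrition and 53 per group (Participants); about 30% reaching biopsy (abstract, Background).

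**1. The plan's own figures.** The 41 cannot be reproduced, because no effect size is printed. Solving backwards with a two-sample t-test, 41 per group at 80% power implies d = 0.626. This is an inference and is used below only as a yardstick.

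The inflation reproduces as 41 × 1.3 = 53.3. A 30% loss requires 41 / 0.70 = 58.6, so 59 per group. With 53 per group, a true 30% loss leaves 53 × 0.70 = 37.1, and power at d = 0.626 is about 76%. Going from 53 to 41 allows for 12/53 = 23% loss. So 80% is not reached even before biopsy is considered.

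**2. Expected dated diagnoses if 30% reach biopsy under usual care (TAU).**
- No attrition: 53 × 0.30 = 15.9, about 16.
- 30% attrition, assumed independent of biopsy: 37.1 × 0.30 = 11.1, about 11.

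For the PERANTARA arm there are two cases: unchanged uptake (16 or 11 again), or uptake raised to 48% (derived in step 4), which gives 53 × 0.484 = 25.7 or 37.1 × 0.484 = 18.0.

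**3. Power for comparing observed intervals (t-test, d = 0.626).**

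| Diagnoses, TAU v PERANTARA | Power |
|---|---|
| 41 v 41 (as planned) | 80% |
| 16 v 26 | 49% |
| 16 v 16 | 40% |
| 11 v 18 | 35% |
| 11 v 11 | 29% |

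The detectable d at 80% power is 1.02 with 16 per arm and 1.26 with 11 per arm. With no attrition, 41/53 = 77% of women would need a dated diagnosis to supply 41 intervals per arm. With 30% attrition only 37 women per arm remain, so 41 cannot be reached.

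**4. Power if undiagnosed women were censored (log-rank, Schoenfeld).** The hazard ratio is an assumption, chosen so that 82 diagnoses (2 × 41) give 80% power: log HR = 2(1.960 + 0.842)/√82 = 0.619, HR = 1.86. A TAU fraction p then implies a PERANTARA fraction 1 − (1 − p)^1.857; for p = 0.30 this is 0.484. Expected diagnoses are n(p + q), where q is the PERANTARA fraction and n is 53, or 37.1 after attrition. Power is Φ(0.619 × √diagnoses / 2 − 1.960).

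| TAU fraction | Diagnoses, no attrition | Power | Diagnoses, 30% attrition | Power |
|---|---|---|---|---|
| 30% (abstract) | 41.6 | 51% | 29.1 | 39% |
| 40% (assumed) | 53.7 | 62% | 37.6 | 47% |
| 50% (assumed) | 64.9 | 70% | 45.4 | 55% |
| 60% (assumed) | 75.1 | 76% | 52.6 | 61% |
| 70% (assumed) | 84.4 | 81% | 59.1 | 66% |

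These figures count any biopsy as a diagnosis and ignore clustering within four hospitals. The outcome requires a breast cancer diagnosis, so benign results would lower the counts further.

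**The case against.** The 30% is an uncited background figure with no time horizon. It describes patients who come to have breast abnormalities checked. Trial participants are suspected of breast cancer and have consented to follow-up, so their biopsy fraction may be higher. This stands. It makes the size of the shortfall uncertain, but it does not restore 80% under the planned attrition: power stays below that level at every TAU fraction from 30% to 70%.

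A reader might infer that the trial will simply yield 11 to 16 dated diagnoses in each arm. The article does not support that as a fact. The 30% fits the usual-care arm best, and an effective intervention should raise uptake in the other arm. The lower figure also needs attrition to be independent of biopsy. If the women lost are mainly those who were never biopsied, about 16 rather than 11 remain under usual care.

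The basis of the 41 is not printed, and a condensed article may leave it to the full protocol. It may have been derived for another outcome or analysis. Some analyses would use every woman: comparing the proportion diagnosed by follow-up, 30% v 60% (assumed rates) with 41 per group gives about 79% power. That shows that power need not depend on dated diagnoses under every analysis. But the article defines the primary outcome as an interval and plans a linear model for it, so this does not rescue the printed claim.

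Finally, how undiagnosed women enter the analysis comes before any power figure. That is true, and it is why the results are given for two analyses and as ranges.

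**Conclusion.** The concern holds in qualified form. The unqualified 80% does not follow from the protocol's own statements, because attrition is the only allowance and the biopsy fraction is left out.

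With 30% biopsied under usual care, that arm supplies about 11 to 16 dated diagnoses against the 41 required, and the PERANTARA arm between 11 and 26 depending on uptake and attrition. Power is then about 29–49% for observed intervals and about 39–51% with censoring. With assumed TAU fractions of 40–70%, time-to-event power is about 47–66% after 30% attrition and 62–81% with none, so 80% is reached only near the top of that range and only if nobody is lost.

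The size rests on d about 0.63, which is inferred, on HR 1.86, which is assumed, and on the 30% applying to enrolled women within the follow-up window. The direction does not depend on the exact fraction. The inflation error is separate and smaller: it alone takes power to about 76%.

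**What to change.** Under Participants, reconcile the sample size with the biopsy fraction in the abstract:

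- Name the outcome and the effect size behind the 41. A value solved backwards, such as d = 0.63, should not be adopted as the design assumption.
- State the assumed fraction reaching a dated diagnosis in each arm, and whether attrition is taken as independent of it.
- Correct the inflation statement: 53 per group covers a 23% loss, and a 30% loss leaves 37.
- In place of the unqualified 80%, print the expected number of dated diagnoses and the resulting power or minimum detectable effect at N = 106, as a range over the stated assumptions.
- State that a non-significant result on diagnosis delay will not be read as absence of effect.

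The cost is one recalculation and a rewritten paragraph. N stays at 106, with no added patients or procedures. The downside is a less favourable stated power.

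### The stated 80% power is not delivered: the analysis is run separately by phase, giving about 50% at best, and no allowance for four randomised hospitals is shown

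*Protocol article*

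**What the plan says.** The Design section describes a trial "with hospitals as the unit of randomisation (clusters"). It adds: "We will include four hospitals in Bandung, Indonesia that have agreed to participate in this study". Each hospital crosses over once: "This study uses two predefined periods". The only link between this design and the sample size is qualitative: "Because every hospital forms its own control, the cross-over design can produce results with a smaller sample size than required with a parallel design".

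The Participants section gives the power statement: "Power calculations suggest a minimum sample size of 41 participants per group (power = 0.80, alpha = .05 two-sided"). It continues: "Taking into account 30% attrition at follow-up, at least 106 participants (53 per group) need to be included". The 106 are split as "53 participants in the Treatment-as-Usual (TAU) control group and 53 participants in the experiment/intervention group". No test, outcome, target difference, standard deviation, ICC or between-period correlation is given.

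The Analysis plan specifies a three-level hierarchical model (repeated measures, persons, clusters). It says that this modelling is done separately for the phase before crossover and the phase after it. It mentions no analysis that combines the two phases.

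**The concern.** The power claim, the design and the analysis do not fit together. The design's economy comes from comparing intervention and control periods within the same hospital. Within a single phase a hospital delivers only one condition, so that comparison does not exist there. What remains is two hospitals against two, with half the women.

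There are also only four randomised units, and the power statement shows nothing that reflects this.

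The 0.80 is the only sample-size justification printed for the primary outcome, and the Discussion makes roll-out conditional on proof of effectiveness. If real power is nearer one half or lower, a non-significant result says little about whether the programme works, yet a reader relying on 80% power could take it as evidence against it.

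**Working it through.** **Inputs from the protocol.** Two-sided alpha 0.05; power 0.80; 41 analysed per group (82 in all); 4 hospitals; 2 periods; 1:1 allocation.

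**Assumed, because the protocol gives no values.** Equal cell sizes; ICC 0.01 to 0.10; CAC (between-period divided by within-period ICC) 0.5 to 1. The 41 per group is taken as actually analysed. Loss of 30% from 53 would leave 53 × 0.7 = 37.1; that is a separate matter and would lower the figures somewhat.

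**Step 1: the plan's own figure.** It cannot be reproduced forward without an effect size. Solving backwards for a two-group comparison of means:
- Normal approximation: d = (1.960 + 0.842) × √(2/41) = 0.619.
- Two-sample t-test: d = 0.626.

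So 41 per group is consistent with an individual comparison at d of about 0.62–0.63.

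**Step 2: both periods together, normal reference.** Women per hospital-period: m = 82/8 = 10.25. Design effect: DE = 1 + (m − 1) × ICC − m × ICC × CAC. The expected test statistic is d/√(2 × DE/41), with d = 0.626.

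| ICC | CAC | DE | Power |
|---|---|---|---|
| 0.01 | 1 | 0.99 | 0.81 |
| 0.10 | 1 | 0.90 | 0.85 |
| 0.01 | 0.5 | 1.04 | 0.79 |
| 0.10 | 0.5 | 1.41 | 0.67 |

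The stated 0.80 lies inside this spread.

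**Step 3: each phase alone, as the Analysis plan says.** Analysed women per arm: 41/2 = 20.5, in two hospitals of 10.25. No own-control term remains, so DE = 1 + 9.25 × ICC. The expected statistic is d/√(2 × DE/20.5), and the ranges below cover d = 0.619 and 0.626. For 2 degrees of freedom: 4 hospital means − 2 arms = 2, critical value 4.30.

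| ICC | DE | Power, normal reference | Power, 2 df |
|---|---|---|---|
| 0 | 1.00 | 0.51–0.52 | 0.22 |
| 0.05 | 1.46 | 0.37–0.38 | 0.17 |
| 0.10 | 1.93 | 0.30 | 0.14 |

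The ICC 0 row hardly depends on the back-solved d. If 41 per group gives 80% power for a comparison of means, the expected statistic is 2.80. Halving the women makes it 2.80/√2 = 1.98, which gives power of about 0.51.

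**Step 4: both periods together, cluster-period analysis.** Eight hospital-period means − 4 hospitals − 1 period − 1 treatment = 2 df. At ICC 0 the expected statistic is 0.626/√(2/41) = 2.84 against a critical value of 4.30, so power is 0.36.

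**The case against.** Several stronger conclusions are tempting, and the protocol does not support them.

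- **That 41 is known to come from a calculation that ignored clustering.** The article names no method and may condense a fuller calculation. An individual t-test needs 34 per group at d = 0.7 and 26 at d = 0.8, so 41 would also fit those effects with design effects of about 41/34 = 1.21 and 41/26 = 1.58. The individual origin is an inference.
- **That clustering by itself pulls power below 80%.** It need not. At CAC 1 the design effect is 1 − ICC, and the crossover slightly gains power. A clear loss needs a low CAC, which is an assumption.
- **That a pooled analysis would have only about one-third power.** That rests on 2 df, and the Analysis plan specifies no such test. If there were no hospital-by-period variation, a patient-level model would have about 82 − 4 − 2 = 76 df and power of 0.80–0.84 over the same ICC range. The 0.36 shows how much depends on the choice of degrees of freedom; it is not an established property of the trial.

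It can also be said that effect sizes and correlations are commonly left to a full protocol, so their absence from an article is no fault in itself. That is accepted. What stands is that the article prints a definite power figure and a definite analysis, and the two do not agree. One could read the by-phase modelling as an addition to a pooled analysis, but the text describes no pooled analysis.

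**Conclusion.** The 80% power is not delivered by the design and analysis as written. The firm ground is the separate analysis of each phase: it gives up the within-hospital comparison used to justify the sample size and leaves about 50% power even with no clustering at all. With ICC 0.05 to 0.10 power is roughly 38% down to 29%, and on 2 cluster-level degrees of freedom it is 0.14 to 0.22.

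These figures rest on equal hospital-period sizes, 41 analysed per group, a comparison of means, and (except at ICC 0 with a normal reference) a back-solved effect of about 0.62–0.63 SD. The ICC values are assumed.

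For an analysis over both periods the conclusion is weaker. The 0.80 cannot be verified. It could be about right with a high between-period correlation and patient-level degrees of freedom, and it is well short under a 2-df cluster-period analysis.

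**What to change.** 1. In the Analysis plan, make the primary analysis a single model over both periods with hospital, period and treatment terms and a small-sample degrees-of-freedom correction. Keep by-phase fits, if wanted, as descriptive.
2. In the Participants section, replace the 0.80 with the power, or the detectable effect, for 106 women under that analysis: 4 hospitals × 2 periods, about 106/8 = 13 women enrolled per cell. State the outcome and target effect, the assumed range for the ICC and the between-period correlation, and the degrees of freedom used.
3. If the resulting power is low, say that the trial estimates the effect with a confidence interval and that a null result is not evidence of no effect.

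The cost is a recalculation, a changed analysis paragraph and probably a less favourable stated figure. No patients are added.

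### 53 women per group do not cover 30% attrition: about 37 remain, against the plan's own minimum of 41

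*Protocol article*

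**What the plan says.** The Participants section under Methods in the protocol article gives the whole sample size argument in two sentences. The first sets the requirement: "Power calculations suggest a minimum sample size of 41 participants per group", with the operating characteristics given as "power = 0.80, alpha = .05 two-sided". The second adds the allowance for loss: "Taking into account 30% attrition at follow-up, at least 106 participants (53 per group) need to be included". The same section splits the total equally, "53 participants in the Treatment-as-Usual (TAU) control group and 53 participants in the experiment/intervention group". The Abstract repeats 106 as the number of patients in the trial.

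The article prints neither the formula that leads from 41 to 53 nor the effect size, standard deviation or test behind the 41.

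**The concern.** The second sentence presents 53 per group as the number that still meets the requirement of 41 once 30% of women have been lost. An allowance of this kind has to be worked from the fraction retained, because attrition acts on the number recruited and not on the number needed. Adding 30% to the required number gives too few, and the gap widens as attrition rises.

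If 53 does not deliver 41, the plan contradicts itself in its headline figure. Readers would take the trial to have 80% power after the expected attrition when, on the plan's own numbers, it does not. The error runs in the unfavourable direction, and it comes before any question about clustering by hospital.

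**Working it through.** **Inputs**, all from the Participants section: minimum 41 per group; power 0.80; alpha 0.05 two-sided; attrition 30% at follow-up; target 53 per group, 106 in total; equal allocation.

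**1. Reproducing the printed figure.**
- Multiplying by one plus the attrition: 41 × 1.3 = 53.3 per group, and 82 × 1.3 = 106.6 in total. Rounded down, these are the printed 53 and 106.
- Dividing by the retained fraction: 41 / 0.70 = 58.6 per group, which does not give 53.

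The printed figure is therefore consistent with multiplication. This is an inference, since no formula is shown, and the next step does not depend on it.

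**2. What 53 per group leaves.**
- 53 × 0.70 = 37.1 per group; 106 × 0.70 = 74.2 in total, against 82 required.
- Shortfall: 41 − 37.1 = 3.9 per group; 3.9 / 41 = 9.5%.

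**3. Attrition that 53 can absorb.**
- 1 − 41/53 = 12/53 = 22.6%, that is, 12 women per group.

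**4. Target that does cover 30%.**
- 41 / 0.70 = 58.6, rounded up to 59 per group, 118 in total, which is 12 more than 106. Check: 59 × 0.70 = 41.3.

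**5. Effect on power.** The effect size is not stated, but it is not needed. Assume an approximately normal test with variance proportional to 1/n that has exactly 80% power at 41 per group. Its expected test statistic at 41 is then 1.96 + 0.84 = 2.80. At 37 per group:
- power = Φ(2.80 × √(37/41) − 1.96) = Φ(0.70) ≈ 0.76.

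A two-sample t-test gives the same answer. With n = 41 and 80% power, the implied standardised difference is d = 0.626. Power at that d is 75.7% with 37 per group and 75.9% with 37.1. If 41 was itself rounded up from just over 40, power at 37 is about 77%. The range is therefore roughly 76% to 77%.

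**6. Effect on the detectable difference.** On the same t-test, the difference detectable with 80% power rises from d = 0.63 at 41 per group to d = 0.66 at 37.

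**The case against.** The strongest objection is that attrition is not the same as loss from the analysis. The 30% refers to follow-up, 12 weeks after the post-intervention assessment. The Procedure section has the Diagnostic Delay Questionnaire and the secondary measures taken at the post-intervention assessment too, and the Analysis plan uses a hierarchical model with repeated measures within person. A woman missing only at 3 months could still contribute data, so the real loss of information may be smaller than 30%. That is fair, and it limits how literally the 76% should be read. It does not reconcile the figures: the Participants section makes no such argument, but sets 41 as the minimum and offers 53 as the number that covers 30% attrition. For the primary outcome, an assessment soon after the intervention may also say little about a woman whose pathological diagnosis has not yet been made.

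Second, the power figure rests on a simple two-group comparison, whereas the trial is a four-hospital cluster cross-over. This also stands in part. The 76% measures the loss in going from 41 to 37 and is not an estimate of the trial's true power. Likewise, a target of 118 repairs only the attrition step and takes the 41 as given.

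Third, the loss is small: about four women per group and about four percentage points of power, with no change to any endpoint or analysis. This is true, but the contradiction remains, and it is cheap to remove.

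**Conclusion.** The point holds. At the plan's own attrition rate, 53 per group leaves 37.1 women, not the stated minimum of 41; covering 30% needs 59 per group, 118 in total. This follows from three printed numbers and needs no assumption about effect size, test or the formula used. Nothing elsewhere in the article corrects it.

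The consequence for power, about 76% instead of 80%, is conditional. It assumes that women lost at follow-up contribute nothing, that variance scales with 1/n, and that 41 per group gives 80% power as the plan says. Whether 41 suits the cluster cross-over design is a separate question, not judged here. The size of the error is modest, but a sample size statement that fails its own minimum is wrong as written and should be corrected.

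**What to change.** Make one of two changes to the sample size sentence in the Participants section.

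- **Restate the figure and keep 106.** For example: with 53 women per group and 30% attrition, about 37 per group remain, giving about 76% power for the difference that 41 per group would detect with 80% power in a simple two-group comparison; 41 per group are retained only if attrition does not exceed 22.6%. This costs one sentence and no patients, and the stated power becomes slightly less favourable.
- **Correct the target.** Set 59 per group, 118 in total, and change the 106 in the Abstract and the group sizes in the Participants section to match. This costs 12 more women. It restores the 41 after attrition and should be described as doing that only, since the basis of the 41 is not shown.

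With either option, give the inflation formula in the text so that the step from the required to the recruited number can be checked.
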